#### Service utilisation data

A cost-consequences approach (CCA) [101] will be used which presents the mean values of each cost category (treatment, other services use) and outcomes in each group together with appropriate measures of central tendency. A CCA does not formally analyse cost-effectiveness. Instead, it provides descriptive information that can be used to generate economic hypotheses for future definitive studies of cost-effectiveness.

#### Qualitative data

Interviews will be conducted with a minimum of ten participants from each of the groups, recruited according to key characteristics (such as previous treatment history), until theoretical saturation is reached. Interviews will explore initial expectations of the intervention, perceived strengths and weaknesses, and suggestions for improvements. Interviews will be recorded, transcribed and analysed using thematic analysis [102].

#### Neuroimaging analysis

##### Structural MRI

Voxel-based morphometry (VBM) analyses will be conducted to evaluate any morphological changes resulting from the series of rTMS.

##### ASL

ASL data will be evaluated in a similar manner to the structural MRI. Following pre-processing, second-level models (such as ANOVAs) will be used to test for an effect of treatment.

##### Resting state MRI

Hypothesis-led seed-based connectivity (DLPFC seed) analyses will be conducted before and after treatment to explore the effect of rTMS on cortico-cortical and thalamo-cortical connectivity. Note, scans will not immediately follow rTMS and therefore will not be affected by acute effects of rTMS.

##### fMRI

Mass univariate analysis will be implemented within SPM12 under the standard generalised linear model (GLM). Contrasts of parameter estimates for separate conditions will provide context-specific maps of neural activity for each participant/session. These will include neural activation to delayed compared to immediate choices in the TD task. In the SST, the main contrasts of interest will include (a) failed stop versus successful stop trials; (b) failed stop versus successful go trials; (c) successful stop versus successful go trials.

##### Common elements

For all modalities, separate images (connectivity maps, task-related activation, structural parameters such as grey matter volume) will be taken forward into a second-level random effects analysis, implemented within SPM12. This will necessitate a factorial ANOVA model, with group (real versus sham) and time (pre versus post), with a significant interaction the primary contrast of interest, as with the clinical and questionnaire data. Significance will be defined as correction for multiple comparisons (*p*FWE < 0.05) at a given height threshold of Z-score of 2.3.

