#### Baseline assessment

Eligible participants will be weighed and asked to complete a battery of questionnaires relating to ED symptomatology and mood, as well as neuropsychological computer tasks that assess behavioural control, attentional bias and food choice behaviour. In addition a one-hour MRI scan will be conducted. The scan will include structural MRI, fMRI (including the Stop Signal Task (SST) and temporal discounting (TD) task), resting state fMRI and arterial spin labelling (ASL).

Once the baseline assessment is complete, participants will be randomly allocated to the treatment (real rTMS) or control (sham rTMS) group.

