##### Neuroimaging outcomes

Magnetic resonance imaging (MRI) measures at baseline and post-treatment include:Structural MRI for neuronavigation of the rTMS coil and for assessing whole-brain structural changes after rTMS using T1 weighted images acquired through a magnetisation-prepared 180 degree radio-frequency pulse and rapid gradient-echo (MPRAGE) sequence (voxel size: 1.1 × 1.1 × 1.2 mm, TR: 7.312 ms, TE: 3.016 ms, number of slices: 196, slice thickness: 1.2 mm, slice gap: 1.2 mm, FOV: 11, flip angle: 11°, matrix: 256 × 256 mm);fMRI involving paradigms assessing inhibitory motor control in a Stop Signal Task (SST) [98] and motivation control, that is, temporal foresight and reward-related decision making in a temporal discounting (TD) task [99, 100]), using an echo planar imaging (EPI) sequence for both tasks (TR: 2,000 ms, TE: 30 ms, number of slices: 40, slice thickness: 3 mm, slice gap: 3.3 mm, number of volumes: SSRT = 193, TD = 363, FOV: 240, flip angle: 75°, matrix: 64 × 64 mm);Resting state fMRI to study neural networks at rest (TR: 2,500 ms, TE: 28 ms, number of slices: 32, slice thickness: 3 mm, slice gap: 4 mm, FOV: 240, flip angle: 80°, matrix: 64 × 64 mm);ASL to obtain a quantitative measure of cerebral blood flow at rest (TR: 5,135 ms, TE: 11.088 ms, number of slices: 56, slice thickness: 3 mm, slice gap: 3 mm, FOV: 240, flip angle: 111°, matrix: 512 × 8 mm).

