#### Clinical outcomes

Analyses will use the intention-to-treat principle. To determine quality, completeness and variability of the outcome measures, descriptive statistical analyses and graphical methods will be used. The size of the treatment effect on each outcome measure (BMI, questionnaires, neuropsychological processes) will be the difference in outcome data between those in the two treatment conditions at post-treatment and follow-up. Group differences will be estimated using linear mixed effects regression models, controlling for the baseline level of the outcome. The aim of the analysis is to establish a suitably precise effect size for the primary outcome in a future large-scale RCT at the post-treatment assessment. Additionally, multiple regression models will permit exploration of the relationship between changes in the varying neuroimaging measures and symptom improvement on questionnaire and task-based outcomes.

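### The primary imaging contrast is a pre/post change comparison, valid but usually less precise than adjusting for the baseline scan, and described as matching clinical models that do adjust for baseline

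*Protocol article*

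**What the plan says.** The Common elements part of the Neuroimaging analysis section sets one second-level model for all imaging: "For all modalities, separate images (connectivity maps, task-related activation, structural parameters such as grey matter volume) will be taken forward" into a "factorial ANOVA model, with group (real versus sham) and time (pre versus post), with a significant interaction the primary contrast of interest". It adds that this is done "as with the clinical and questionnaire data". Inference is on maps with family-wise error correction at 0.05, "at a given height threshold of Z-score of 2.3". No baseline covariate is mentioned there or in the modality-specific paragraphs.

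Scans are taken twice. The Neuroimaging outcomes section reads "Magnetic resonance imaging (MRI) measures at baseline and post-treatment include", and the Follow-up section excludes MRI. The first scan precedes allocation. Under Baseline assessment the article says "In addition a one-hour MRI scan will be conducted" and then "Once the baseline assessment is complete, participants will be randomly allocated to the treatment (real rTMS) or control (sham rTMS) group".

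For the clinical data, the Clinical outcomes part of the Analyses section says "Group differences will be estimated using linear mixed effects regression models, controlling for the baseline level of the outcome".

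**The concern.** There are two linked problems. First, the imaging section claims the same approach as the clinical analysis, but the clinical analysis treats baseline as a covariate while the imaging model treats it as one of two outcome occasions. An analyst cannot follow both descriptions as written.

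Second, with two occasions the interaction compares change scores, which fixes the slope on the baseline scan at 1. When the true slope is lower, the change score subtracts too much of the baseline and keeps noise that a fitted slope would remove. Neural mechanisms are among the trial's stated aims, and about 40 patients will carry them, so precision is scarce. The baseline scan is already collected before randomisation and is therefore a legitimate covariate.

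**Working it through.** **Plan's own figure.** The article states no power or precision for imaging, so there is none to reproduce. The Sample size section gives 22 per arm and 10% attrition: 22 × 0.9 = 19.8, so 20 per arm is used below, in line with the target of 40.

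**Assumptions not in the article.** Equal variance (SD = 1) at both scans, normally distributed values, complete pairs, and a pre-post correlation rho, varied from 0.3 to 0.95.

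**Step 1: what the interaction estimates.** With two groups and two times it is (post − pre, real) − (post − pre, sham), the difference in mean change.

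**Step 2: variance per patient.**
- Change score: 2(1 − rho).
- Baseline-adjusted, slope known: 1 − rho².
- Ratio, adjusted to change: (1 + rho)/2.

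**Step 3: allow for estimating the slope.** With 20 per arm the pooled within-group degrees of freedom are 38. Estimating the slope multiplies the adjusted variance on average by 1 + 1/(38 − 2) = 37/36 = 1.028. The ratio becomes (37/36)(1 + rho)/2.

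| rho | Change | Adjusted, slope known | Adjusted, slope estimated | Ratio | Variance cut |
|---|---|---|---|---|---|
| 0.3 | 1.40 | 0.910 | 0.935 | 0.67 | 33% |
| 0.5 | 1.00 | 0.750 | 0.771 | 0.77 | 23% |
| 0.7 | 0.60 | 0.510 | 0.524 | 0.87 | 13% |
| 0.9 | 0.20 | 0.190 | 0.195 | 0.98 | 2% |
| 0.95 | 0.10 | 0.0975 | 0.100 | 1.00 | none |

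Break-even is at rho = 2(36/37) − 1 = 0.946. A simulation of 8,000 trials per rho gave ratios of 0.67, 0.76, 0.87 and 0.98 at rho = 0.3, 0.5, 0.7 and 0.9. Under no effect, both estimators averaged close to zero.

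**Step 4: where the lost precision comes from.** With the slope known, 2(1 − rho) − (1 − rho²) = (1 − rho)². The chance baseline difference between arms has SD √(2/20) = 0.316, and the change score carries −(1 − rho) times that difference. The variance of this carried-over term is (1 − rho)² × 2/20, which is exactly the gap. At rho = 0.5, a baseline difference of one standard error moves the change-score estimate by 0.5 × 0.316 = 0.16 SD. The imbalance and the lost precision are therefore the same quantity.

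**Step 5: illustration as power.** One regional measure, two-sided 5%, rho = 0.5, noncentral t:
- 0.8 SD effect. Change: 0.8/√(1.00 × 0.1) = 2.53 on 38 df, power 69%. Adjusted: 0.8/√(0.771 × 0.1) = 2.88 on 37 df, power about 80%.
- 0.5 SD effect. Change: 1.58, power 34%. Adjusted: 1.80, power about 42%.

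**The case against.** The strongest reply is that nothing here is invalid. The interaction test keeps its type I error, the estimate is unbiased over randomisation, and a group-by-time model is conventional in SPM12. The trial is a feasibility study with no primary outcome, no imaging power and tentative hypotheses. The imaging aims are worded as changes, and the article also plans regressions relating imaging change to symptom improvement, so they do not rest on this contrast alone. All of that stands, and it limits the weight of the point.

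It is also fair that the size of the gain depends on an assumed correlation. For very repeatable measures, as structural volumes may be, there is little or nothing to gain. A reader might infer that the change score is never the more precise choice. At this sample size that fails above rho of about 0.95.

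A reader might also infer that chance baseline imbalance biases the imaging result on top of the loss of precision. Step 4 shows that it does not: over repeated randomisation it is the same variance. Finally, the power levels above might be read as the power of this trial's imaging analysis. They are not, because the planned inference is on family-wise-error-corrected maps.

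The objection does not remove the mismatch between the imaging and clinical sections. Nor does it give a reason for setting aside, for imaging alone, an adjustment that the article already adopts for the clinical outcomes.

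**Conclusion.** The point holds as one of efficiency and consistency, not validity. The imaging section describes its contrast as the one used for the clinical data, and the clinical section describes a different, baseline-adjusted model. Under equal variances and 20 per arm, the planned interaction is less precise than baseline adjustment for any rho below about 0.95. The loss is material at rho of 0.3 to 0.5, modest at 0.7 and trivial at 0.9. The article supplies no correlation, so where each modality falls in that range is unknown. No stated figure is overturned. Because the imaging is exploratory, this is a worthwhile improvement rather than a critical defect.

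**What to change.** In Common elements, define the primary imaging contrast as the real-versus-sham difference in the post-treatment image, with the same patient's baseline value as a voxel-wise covariate. If voxel-wise covariates are impractical in SPM12, apply the same model to pre-specified regional values, such as the DLPFC for task fMRI, ASL and seed connectivity. Name the regions in advance and keep multiplicity control across them. Retain the group-by-time ANOVA as a sensitivity analysis. Reword the comparison with the clinical and questionnaire data so that it agrees with the Clinical outcomes part of the Analyses section. For highly repeatable structural measures the switch is optional.

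The cost is one residual degree of freedom and some set-up time, either for a tool that takes voxel-wise covariates or for extracting regional values. No further patients or scans are needed.

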#### Sample size

As this is a feasibility study, no a priori sample calculation has been conducted. This study aims to provide effect sizes on which future large-scale studies can be powered. Total sample sizes of *N* = 24–50 have been recommended for feasibility trials with outcomes measured on a continuous scale, mainly because estimates of the standard deviation for normally distributed variables tend to stabilise around this size [65, 66]. We have chosen a sample size of *N* = 40 (that is, at the upper end recommended for feasibility trials). Assuming the attrition to follow-up rate is a = 0.10 (as found in our previous AN trials [15, 67], [name] et al., unpublished observations and applying an attrition correction factor of 1/(1-a), we will need a total sample size of *N* = 44 (22 participants per group).

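### The protocol names two different contrasts for the clinical and questionnaire outcomes, and the interaction named in the imaging section is the less precise one

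*Protocol article*

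**What the plan says.** Three places in the protocol article bear on this.

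- **Analyses, Clinical outcomes.** The size of the treatment effect on each measure "will be the difference in outcome data between those in the two treatment conditions at post-treatment and follow-up". The method follows: "Group differences will be estimated using linear mixed effects regression models, controlling for the baseline level of the outcome". No interaction is mentioned. The stated purpose is estimation: "The aim of the analysis is to establish a suitably precise effect size for the primary outcome in a future large-scale RCT", with post-treatment as the time point.
- **Neuroimaging analysis, Common elements.** The second-level imaging model crosses group with time, where time has the two levels pre and post. The contrast is then named, and its reach is extended beyond imaging: "with a significant interaction the primary contrast of interest, as with the clinical and questionnaire data".
- **Sample size.** The target is 40 patients, "that is, at the upper end recommended for feasibility trials", raised to 44 (22 per group) by "applying an attrition correction factor of 1/(1-a") with a = 0.10.

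The protocol does not give the correlation between baseline and post-treatment scores for any outcome.

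**The concern.** The two sections describe the analysis of the same outcomes and do not agree. In the model of the Clinical outcomes section, baseline sits on the right-hand side as a covariate, so the outcome times are post-treatment and follow-up only. In the model of the Common elements section, baseline is one of the two levels of time and so sits on the outcome side. A pre-versus-post interaction cannot be formed in the first model, and the second has no follow-up level. An analyst has to choose, and the article does not say which statement governs.

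The choice affects results that the trial exists to deliver. The Aims section wants effect sizes and standard deviations for a later sample size calculation, and the Feasibility section lists effect sizes among the criteria for progression. There are many outcomes and no primary one. If the contrast is left open, it could be chosen outcome by outcome once the data are seen.

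**Working it through.** **The plan's own figure.** 40/(1 − 0.10) = 44.4, against the stated 44. Rounding up would give 45; the difference is immaterial here. The comparison below uses 20 per arm, the number expected after attrition.

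**Inputs.** From the protocol: randomised two-arm design, equal groups, n = 20 per arm analysed. Assumed, because the protocol does not state them: outcome SD of 1 at both times, correlation r from 0.3 to 0.9, and, where significance is discussed, a true effect of 0.5 SD and a two-sided 5% level. The post-treatment contrast of the mixed model is treated as an analysis of covariance with complete data.

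**Do the two contrasts have the same target?** With two groups and two times, the group-by-time interaction is the difference between arms in mean change. Randomisation makes the expected baseline difference zero, so the expected difference in change equals the expected baseline-adjusted difference at post-treatment. In 20,000 simulated trials at each r with a true effect of 0.5, the mean of both estimates was 0.50 throughout.

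**Precision.**

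- Interaction: SE = √[2(1 − r) × 2/n]
- Baseline-adjusted: SE = √[(1 − r²) × 2/n]
- Variance ratio: 2(1 − r)/(1 − r²) = 2/(1 + r)

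At r = 0.5 these are √(1.0 × 0.1) = 0.316 and √(0.75 × 0.1) = 0.274, with a ratio of 2/1.5 = 1.33.

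**Gap between the estimates in one trial.** The two differ by about (1 − r) times the chance baseline imbalance, whose SD is √(2/20) = 0.316. At r = 0.5 this is 0.5 × 0.316 = 0.158. The simulation gives 0.165, slightly more because the regression slope is estimated.

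| Assumed r | SE, interaction | SE, adjusted | Variance ratio | SD of gap, formula | SD of gap, simulated | Only one of the two significant |
|---|---|---|---|---|---|---|
| 0.3 | 0.374 | 0.302 | 1.54 | 0.221 | 0.228 | 20% |
| 0.5 | 0.316 | 0.274 | 1.33 | 0.158 | 0.165 | 17% |
| 0.7 | 0.245 | 0.226 | 1.18 | 0.095 | 0.102 | 14% |
| 0.9 | 0.141 | 0.138 | 1.05 | 0.032 | 0.040 | 3% |

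**What the same ratio means for a future trial.** For a true effect of 0.5 SD, 80% power and a two-sided 5% level, n per arm = 2(1.96 + 0.84)² × V/0.5², with V = 2(1 − r) for the interaction and 1 − r² for the adjusted analysis. This gives 88 against 58 at r = 0.3, 63 against 48 at r = 0.5, 38 against 33 at r = 0.7, and 13 against 12 at r = 0.9.

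**The case against.** The best defence is that the section written for the clinical outcomes is clear and specific, and that the conflict comes from one trailing clause in a section on imaging. A sensible analyst would follow the dedicated section. The trial is a feasibility study with no primary outcome, its clinical analysis is for estimation, and effect size is only one of several progression criteria. The penalty also depends on a correlation that the protocol does not give, and at r = 0.9 it is negligible. All of this stands and limits the seriousness of the point. It does not remove the contradiction: the clause names the clinical and questionnaire outcomes expressly, and the article does not say which statement prevails.

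Three stronger readings are tempting, and the protocol does not support them.

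- A reader might infer that the two analyses estimate different things. Under randomisation they do not; they differ in precision and in how they treat chance baseline imbalance.
- A reader might infer that the interaction would miss a benefit that is sustained. That needs an interaction between post-treatment and follow-up. The Common elements section defines time as pre versus post, which rules it out.
- A reader might infer that the imaging ANOVA ignores within-patient correlation, because no subject factor is named; with independent errors the SE would be inflated by 1/√(1 − r), or 41% at r = 0.5. The article describes a random-effects second-level analysis and nowhere states independent errors, and such model detail is commonly left to the full protocol. Replacing the ANOVA by a comparison of post-minus-pre images would gain nothing, since that comparison is the same interaction.

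**Conclusion.** The clause is wrong as written and should be fixed. The protocol gives two contrasts for the same clinical and questionnaire outcomes, and they cannot both be the planned one. The target at post-treatment is the same, so there is no question of bias. The cost of following the imaging clause is a variance 5% to 54% larger over the assumed range of r from 0.9 down to 0.3. With 20 per arm it also means estimates that can differ noticeably in the same trial, and a different significance result in 3% to 20% of trials if the true effect is 0.5 SD. These sizes rest on equal SDs at both times, complete data and the assumed correlations. The contradiction itself rests only on the text.

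**What to change.** In the Common elements part of the imaging analysis, delete the clause that extends the interaction to the clinical and questionnaire outcomes. In the Clinical outcomes part of the Analyses section, add one sentence: the clinical effect is the baseline-adjusted group difference from the mixed model at post-treatment, reported separately at follow-up, and is not an interaction test. The imaging analysis can stay as it is.

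The cost is two sentences. No new data, assessments or patients are needed, and the analysis workload does not change, because the baseline-adjusted model is already planned.

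### The imaging significance rule (pFWE < 0.05 at a height of Z = 2.3, all modalities including VBM) appears to be random-field cluster inference and does not reliably hold 5% family-wise error

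*Protocol article*

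**What the plan says.** Under Neuroimaging analysis, Common elements, the article applies one second-level procedure to everything. It states the scope first: "For all modalities, separate images (connectivity maps, task-related activation, structural parameters such as grey matter volume". It then says what happens to these images, namely that they "will be taken forward into a second-level random effects analysis, implemented within SPM12". The model is a "factorial ANOVA model, with group (real versus sham) and time (pre versus post), with a significant interaction the primary contrast of interest". The error rule follows: "Significance will be defined as correction for multiple comparisons". The level is pFWE < 0.05, and it applies "at a given height threshold of Z-score of 2.3".

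The Structural MRI subsection places VBM under this rule: "Voxel-based morphometry (VBM) analyses will be conducted to evaluate any morphological changes resulting from the series of rTMS". No separate rule for VBM, correction for non-stationary smoothness or permutation method is named. Whether the interaction is tested in one direction or both is not stated.

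**The concern.** Z = 2.3 is a low height at which to form clusters. Random-field cluster p-values are an approximation for high thresholds, and they assume a Gaussian-shaped spatial autocorrelation and the same smoothness everywhere. If the autocorrelation has a longer tail, or some regions are smoother than others, chance clusters at a low height are larger than the theory expects. The printed cluster p of 0.05 is then not a 5% error rate. Varying smoothness is a particular worry for VBM, which gets the same rule as the rest.

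Significant group-by-time clusters are meant to inform the Aims on neural mechanisms of response, and the abstract looks to the results for candidate biomarkers. Clusters that appear by chance more often than stated would weaken both.

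**Working it through.** **Inputs from the article.** Nominal FWE 0.05, height Z = 2.3, SPM12, group-by-time interaction (Common elements). The Sample size section says "We have chosen a sample size of" 40, inflated for 10% attrition: 40/0.9 = 44.4, consistent with the stated 44. I take 40 analysable participants as 20 per arm. The 2 x 2 interaction is then a two-sample t test on post-minus-pre images with 20 + 20 - 2 = 38 df.

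**Assumptions, not in the article.** Mask, smoothness and shape of the autocorrelation, as listed in the table.

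**Step 1: what the height means.** 1 - Phi(2.3) = 0.0107 one-sided, or t = 2.40 on 38 df. In an assumed volume of 38 x 38 x 38 = 54,872 voxels of 3 mm, chance alone puts about 54,872 x 0.01072 = 588 voxels above this height in each direction. It cannot be a voxel-level FWE threshold. Combined with an FWE correction, it makes sense only as the height that defines clusters.

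**Step 2: the cluster p-value.** The random-field formula for a cluster of k resels in D = 3 dimensions is

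P = 1 - exp{ -E[m] exp(-phi k^(2/D)) }, with phi = (Gamma(D/2 + 1) / E[k])^(2/D).

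E[m] is the expected number of clusters, from the t-field Euler characteristic densities. E[k] is the expected cluster size. Smoothness is one global value estimated from the residuals.

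**Step 3: can the stated 5% be reproduced?** Not by formula, because the article gives no smoothness or mask. It was checked by null simulation in two sets with different settings. Set A used the volume above, with 500 replicates (400 for mild tails) and a stricter height of Z = 3.1 for comparison. Set B used a 41,928-voxel mask, 400 replicates and Z = 3.09. Each direction was tested at a nominal 5%.

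| Assumed null field | Z = 2.3: one direction / both | Z about 3.1: one direction / both |
|---|---|---|
| A: stationary Gaussian, FWHM 8 mm | 1.4% / 2.8% | 1.3% / 2.6% |
| A: stationary Gaussian, FWHM 10 mm | 1.7% / 3.4% | 2.0% / 4.0% |
| B: stationary Gaussian | 2.25% / - | 2.0% / - |
| A: mild long tail (10% of variance at 20 mm, rest 8 mm) | 5.6% / 11.0% | 2.2% / 4.5% |
| A: stronger long tail (25% at 20 mm, rest 8 mm) | 14.0% / 27.0% | 5.0% / 10.0% |
| B: mixed short- and long-range | 15.25% / - | 7.25% / - |
| A: one third of volume at 16 mm, rest 8 mm | 29.2% / 51.2% | 14.4% / 27.0% |
| B: halves at FWHM 2 and 5 voxels | 46.25% / - | 27.25% / - |

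The largest Monte Carlo standard error in the one-direction figures is about sqrt(0.4625 x 0.5375 / 400) = 0.025, or 2.5 points.

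**Step 4: why varying smoothness does the most harm.** In set A the global estimate for that field averaged 9.22 mm. In the 16 mm region a cluster is therefore credited with about (16/9.22)^3 = 5.2 times its proper size in resels. A higher height shrinks the clusters but leaves this mis-scaling in place.

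**The case against.** **The reading is inferred.** The words cluster and parametric do not appear in Common elements. A reader might infer that the article declares parametric cluster inference; it does not. Naming SPM12 names software, and a fuller plan could hold a permutation check or a non-stationarity correction. This stands as a limit on the wording. It does not remove the point: the error rule is stated, not left out, and cluster extent is its only coherent meaning. If something else was intended, the sentence needs rewriting anyway.

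**The excess comes from assumed fields.** Under the theory's own assumptions the rule is conservative, and the 46% case uses an abrupt split of the brain. Nothing in the article shows how far this trial's difference images depart from the ideal. A reader might infer one inflated rate for this trial; the documents support only a range.

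**Combining maps.** A reader might multiply one inflated rate over the seven or so planned maps to get an overall chance of a false finding. That is not supported. The three stop-signal contrasts are linearly dependent: failed stop minus successful go is the sum of the other two. The rate for each map is unknown, and multiplicity across maps is a separate question that would remain even at a true 5%.

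**Imaging is secondary to the trial's purpose.** The progression criteria under Analyses, Feasibility are recruitment, retention, treatment completion, acceptability and effect sizes of treatment outcomes. The likely future primary outcomes are EDE-Q and DASS-21 (Outcome measures). The imaging hypotheses are called tentative and much of the work exploratory. This stands in full and sets the weight of the point.

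**Conclusion.** The concern holds in a limited form. The rule appears to be random-field cluster-extent inference with a cluster-forming p of about 0.011, and it does not reliably deliver the stated 5%. Per direction, the simulated error was about 1-2% in ideal stationary fields, about 6-15% with long-tailed autocorrelation and about 29-46% with varying smoothness. These figures rest on 20 images per arm, one global smoothness estimate, and assumed smoothness and autocorrelation.

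A reader might also infer that a stricter height alone settles the matter. It does not: at Z of about 3.1 the long-tailed cases fall to about 2-7% per direction, but varying smoothness still gives about 14-27%.

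The sentence should be changed, but no main conclusion of the trial depends on it. The effect is confined to the exploratory claims about neural mechanisms and potential biomarkers.

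**What to change.** Replace the significance sentence with permutation-based FWE inference at two-sided 0.05 for all modalities. Form one post-minus-pre image per participant, exchange arm labels, and use TFCE or maximum cluster size with a cluster-forming p < 0.001. Do not use stationary parametric cluster size for VBM.

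If parametric cluster inference is kept for fMRI or ASL, form clusters at p < 0.001, split alpha over the two directions, and state that this reduces the inflation without guaranteeing 5%.

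The change should be dated and made before images are analysed by arm, so that the rule stays pre-specified. It costs one sentence, computing time and some sensitivity to weak, diffuse effects. Recruitment, scanning and sample size do not change.
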